# Prospective randomized trial evaluating mandatory second look surgery with HIPEC and CRS vs. standard of care in patients at high risk of developing colorectal peritoneal metastases

**DOI:** 10.1186/1745-6215-11-62

**Published:** 2010-05-25

## Abstract

**Background:**

The standard of care for colorectal peritoneal carcinomatosis is evolving from chemotherapy to cytoreductive surgery (CRS) with hyperthermic intraperitoneal chemotherapy (HIPEC) for patients with disease limited to the peritoneum. Peritoneal carcinomatosis from colorectal cancer treated with chemotherapy alone results in median survival of 5 to 13 months, whereas CRS with HIPEC for early peritoneal carcinomatosis from colorectal cancer resulted in median survival of 48-63 months and 5 year survival of 51%.

Completeness of cytoreduction and limited disease are associated with longer survival, yet early peritoneal carcinomatosis is undetectable by conventional imaging. Exploratory laparotomy can successfully identify early disease, but this approach can only be justified in patients with high risk of peritoneal carcinomatosis. Historical data indicates that patients presenting with synchronous peritoneal carcinomatosis, ovarian metastases, perforated primary tumor, and emergency presentation with bleeding or obstructing lesions are at high risk of peritoneal carcinomatosis. Approximately 55% of these patient populations will develop peritoneal carcinomatosis. We hypothesize that performing a mandatory second look laparotomy with CRS and HIPEC for patients who are at high risk for developing peritoneal carcinomatosis from colorectal cancer will lead to improved survival as compared to patients who receive standard of care with routine surveillance.

**Methods/Design:**

This study is a prospective randomized trial designed to answer the question whether mandatory second look surgery with CRS and HIPEC will prolong overall survival compared to the standard of care in patients who are at high risk for developing peritoneal carcinomatosis from colorectal cancer (CRC). Patients with CRC at high risk for developing peritoneal carcinomatosis who underwent curative surgery and subsequently received standard of care adjuvant chemotherapy will be evaluated. The patients who remain without evidence of disease by imaging, physical examination, and tumor markers for 12 months after the primary operation will be randomized to mandatory second look surgery or standard-of-care surveillance. At laparotomy, CRS and HIPEC will be performed with intraperitoneal oxaliplatin with concurrent systemic 5-fluorouracil and leucovorin. Up to 100 patients will be enrolled to allow for 35 evaluable patients in each arm; accrual is expected to last 5 years.

**Trial Registration:**

ClinicalTrials.gov ID: NCT01095523

## Background

In the United States, approximately 108,070 patients are diagnosed with colon cancer and 40,740 patients with rectal cancer per year (colorectal cancer = CRC) [1]. 49,970 patients die from CRC per year. Initially, peritoneal carcinomatosis (PC) commonly occurs without systemic dissemination. In one study of the 3019 patients reviewed with CRC, 349 (13%) had carcinomatosis [2]. 214 (61%) patients had synchronous disease and 135 (39%) patients had metachronous disease. 58% of synchronous PC was limited to the peritoneal cavity and 64% of these patients had localized disease to one quadrant [2]. Overall, recurrences are limited to the peritoneum in 25% of patients with CRC [3]. Approximately 8000 patients are diagnosed with synchronous PC in the United States per year.

Modern chemotherapy has improved survival of patients with PC, but despite increased response rates and increased median survival, few patients experience long term survival with chemotherapy alone. The median survival of patients with PC without systemic dissemination was 7 months for the 3019 patients reported above [2]. Another study prospectively evaluated 45 patients with PC who achieved a median overall survival of 6 months [3]. 118 patients in a French registry showed a median overall survival of 5.2 months [4]. Most of these patients received systemic 5-FU and leucovorin-based regimens. Although multiple reports of metastatic disease demonstrate an increased survival with current chemotherapeutic regimens [5-10], Elias et al. reports the only series that follows patients with PC without systemic dissemination treated with current standard of care systemic chemotherapy regimens of FOLFOX (5-fluorouracil (5-FU), leucovorin, and oxaliplatin) and FOLFIRI (5-fluorouracil (5-FU), leucovorin, and irinotecan). The authors report a median survival of 23.9 months and 2-, and 5-year survival of 65% and 13%, respectively [11]. Clearly, patients have benefited from better systemic regimens, but at best, survival is only 13% at five years for this group of patients treated with modern systemic chemotherapy alone.

The prognosis of patients with PC has significantly improved with the combination of cytoreductive surgery (CRS) and hyperthermic intraperitoneal chemotherapy (HIPEC) [11-13]. The 5-year overall survival ranges from 40 - 51%. The technique has previously been described as peritonectomy, hyperthermia, and resection of intrabdominal disease as necessary [14-16]. Hyperthermia has been shown to increase the cytotoxicity of chemotherapy [17,18]. CRS and HIPEC initially began as the treatment for appendiceal malignancy and malignant peritoneal mesothelioma [19-21]. In 2006, this procedure was declared the standard of care by the National Cancer Institute for ovarian PC based on the results of a phase III study [22]. In the past 8 years, two randomized clinical trials (RCT), one nonrandomized comparative study, and 11 observational studies have been reported for colorectal carcinomatosis and summarized in a comprehensive review article by Yan et al [23].

Verwaal et al [24] performed a RCT of CRS and HIPEC versus systemic chemotherapy alone which demonstrated a significant survival benefit with increase in median survival of 22 mo. versus 12 mo. and 2-year survival of 44% versus 22%, respectively. Even though this trial demonstrates a clear benefit, the systemic therapy with 5-FU and leucovorin is an outdated regimen compared to current treatment of FOLFOX or FOLFIRI. In addition, the HIPEC drug was mitomycin-C which is not the most effective drug against CRC. Regardless, the patients who underwent intent-to-treat randomization and received CRS and HIPEC achieved a significant survival advantage (p = 0.032). For the patients who received an R0 resection, the 2-year survival was 60%. A multi-institutional registry [25] of 506 patients who underwent CRS and HIPEC for CRC with PC demonstrated a 1-, 3-, and 5-year survival of 72%, 39%, and 19%, respectively with a median survival of 19 months. Again, similar to the RCT data, patients with complete CRS achieved the highest survival. The patients who underwent R0 resection achieved a 1-, 3-, and 5-year survival of 87%, 47%, and 31%. The ten single institutional case-series reviewed by Yan et al. [23] demonstrated overall median survivals from 13 to 29 months and 1-, 2-, 3-and 5-year survival rates of 55-75%, 31-64%, 21-28%, and 11-19%, respectively. Clearly, with one trial of level 1 data, another with good level 2 data, and multiple case series reporting excellent survivals, CRS with HIPEC shows promise to become the standard of care for CRC with PC.

Unfortunately, PC is usually detected late in the course of disease secondary to late presentation of symptoms and difficulty with detection based upon imaging techniques and tumor markers. Once symptomatic disease develops, complete resection is more difficult to achieve. The only reliable means of detection is repeat laparotomy, but this operation cannot be justified in all patients with CRC. High risk group of patients who may benefit [26-28] have been defined after a prospective phase II trial as those patients with synchronous limited PC at initial operation, synchronous ovarian metastases, perforated primary tumors, T4 lesions that required adjacent organ resection, and emergency presentation for obstructing and bleeding lesions [26]. 62% of patients with limited PC at presentation, 75% of patients with ovarian metastases, 15% of patients with perforated CRC, and 19% of patients with T4 lesions that required resection of adjacent organs will develop PC [2].

Given the impact on survival with CRS and HIPEC, Elias et al. [26] performed a prospective study to analyze the outcomes with mandatory second-look surgery (MSLS) for patients at high-risk for recurrence as stated above. All patients were NED based upon symptoms, tumor markers, CT, and PET. Every patient had appropriate primary resection with adjuvant FOLFOX or FOLFIRI as the current standard of care. Six months after the last chemotherapy, MSLS was performed. Macroscopic PC was found in 55% of the patients (16/29) who were asymptomatic with negative evaluation. All of the patients with recurrence were treated with CRS and HIPEC. No post-operative mortality occurred. With a median follow-up of 27 months, of the 16 patients with recurrent peritoneal carcinomatosis, 8 (50%) remained NED, 4 (25%) relapsed with PC (2 with distant metastases), and 4 (25%) developed visceral metastases. Most importantly, this study revealed that high-risk patients with recurrent PC are often detected only at laparotomy despite appropriate surveillance and that the early detection of disease may result in complete CRS compared to CRS of symptomatic disease or disease detected by imaging.

Chemotherapeutic drugs used for intra-operative management are based on the most effective systemic regimens which also demonstrate good results regarding intraperitoneal delivery. Systemic oxaliplatin has demonstrated significant activity against metastatic CRC with an objective response rate of 24% as a single agent and 55% in combination with 5-FU and leucovorin (FOLFOX) [8,29,30]. FOLFOX is one of the first line standard of care regimens for metastatic CRC. Oxaliplatin is currently the most studied intraperitoneal drug [31-33] and it is also potentiated by hyperthermia and it works at all stages of cell division [17,34].

In summary, for approximately 50% of patients who develop PC from CRC, a complete resection may be potentially curative. Patients with high-risk primary CRC have an incidence of PC greater than 50%, yet modern imaging and tumor or serum markers fail to detect recurrence at an early stage. We hypothesize that MSLS with CRS and HIPEC in patients who are at high risk for recurrent PC will lead to improved survival compared to standard surveillance. Therefore, a prospective randomized trial has been designed to evaluate MSLS with CRS and HIPEC versus treatment of PC once disease is detected, during routine surveillance, by imaging or symptoms.

## Methods

### Ethical Approval

The Mandatory Second Look Surgery (MSLS) for high Risk Colorectal Cancer trial was approved by the Institutional Review Board (IRB) of the National Cancer Institute, National Institutes of Health, Bethesda, Maryland.

### Design

This study is a randomized controlled trial. The trial schema is illustrated in Figure 1. The study will be performed at the Clinical Center of the NIH by the Surgery Branch of the NCI in Bethesda, Maryland, USA. Patients who have undergone curative surgical resection for the primary CRC tumor, are at high risk for development of PC, have completed at least 3 months of standard of care systemic therapy, and show no evidence of disease may be enrolled and randomized to receive either standard of care surveillance (SC) or mandatory second-look surgery (MSLS) followed by CRS and HIPEC. Randomization will occur between 11 - 14 months after the primary operation to allow flexibility in enrollment and accrual without effect on design.

**Figure 1 F1:**
[figure not shown]
**Trial schema**.

### Stratification and Randomization

Registration of patients onto this study will take place within 24 hours of the patient signing the consent by faxing a completed eligibility checklist to the Central Registration Office. This trial will consist of three stages: Lead-in Stage includes the time period from 3 months to 14 months following resection. Patients who present for evaluation prior to month 11 post resection will be enrolled in this stage prior to randomization. Stage 1 includes MSLS with HIPEC and CRS and the recovery period. Patients who are randomized to receive surgical intervention will be entered on stage 1. Stage 2 is the follow up period. Patients who are randomized to surveillance will be directly entered on stage 2; patients who are randomized to the MSLS arm will be entered on stage 2 upon recovery from the operative procedure. After 11-14 months following primary resection, the patients will be stratified and randomized by the Central Registration Office to undergo MSLS with HIPEC and CRS or standard-of-care surveillance (SC) without surgery. The Central Registration Office will notify the study coordinator of the results of randomization. Patients must be randomized within 2 weeks of the baseline imaging studies. Patients who are randomized to the MSLS arm must be treated within 2 weeks of randomization.

Patients will be stratified according to two factors: 1: Presenting with PC, which was completely resected, and/or ovarian metastases (incidence of recurrent PC > 60%) vs. presenting with tumor perforation, T4 lesions that required adjacent organ resection, and/or emergency presentation with bleeding or obstructing lesions (incidence of recurrent PC < 40%), and 2: Receiving adjuvant chemotherapy for less than 6 months vs. > 6 months. This will generate 4 strata.

### Statistics

The primary objective of the trial is to determine if there is a difference in overall survival among patients who are at high risk for CRC PC and are randomized to receive either SC alone or MSLS with HIPEC and CRS when indicated.

Based upon results in the literature, patients who would be eligible to be randomized on this trial and who receive SC alone would be expected to have an estimated 25% 5-year survival from the date of randomization. The goal of this study will be to determine if the use of a MSLS with HIPEC and CRS will result in patients having survival that is associated with an increase to 50% 5-year survival. Following registration, patients who are eligible for randomization will be randomized between SC and MSLS with HIPEC and CRS and followed for survival. Patients will be stratified for synchronous peritoneal carcinomatosis and ovarian metastasis vs. perforated primary and emergency with bleeding or obstruction, and prior chemotherapy ≤ 6 months vs. >6 months. Kaplan-Meier curves and a two-tailed log-rank test will be the primary analysis methods. Assuming exponential survival curves, the hazard rate for the systemic therapy is 0.0231, or approximately a 2.3% probability of dying each month when the 5-year survival probability is 25%. If we assume that the MSLS arm will have an associated survival of 50% at 5 years, this survival corresponds to a hazard rate of 0.0116, and the resulting hazard ratio for the comparison of the two overall survival curves would be 1.991. Following the principles of a phase 2.5 design, to compare these curves and detect a difference with a 0.10 one-tailed log-rank test, a total of 35 evaluable subjects per arm (70 total) will need to be randomized over a five year period, followed for an additional two years from the date of entry of the last patient, and observation of 38 total deaths in order to have 80% power to compare the curves.

It is expected that 80% of registered patients will be eligible for the randomization. Thus, in order to enroll 70 randomized patients, a total of up to 100 evaluable patients may be enrolled. The patients who present prior to 11 months will be enrolled in the lead-in stage in which some patients may develop symptomatic or image-detected disease. These patients will not be eligible for randomization, but the number of randomized patients relative to enrolled patients will be noted in order to determine the denominator of patients who develop peritoneal recurrence within the first year of treatment. Registration will be permitted to continue until 70 patients have been randomized, and thus it is possible that up to 5-10 additional patients beyond 70 may be randomized. This will permit a very small increase in power. Patients will be analyzed as randomized; only patients found to be grossly inevaluable for any reason will not be included in the final analysis once randomized.

Progression-free survival will also be evaluated using Kaplan-Meier curves and a two-tailed log rank test, as a secondary endpoint. In addition, a prognostic factor evaluation using Cox proportional hazards modeling will take place after the study has concluded in order to identify if there are factors which can be identified that are associated with overall or progression-free survival in patients randomized to treatments on this trial; this analysis will be interpreted as a secondary endpoint.

It is expected that 20 patients per year can be accrued onto this trial, and thus accrual will be completed in approximately 5 years. Allowing for a very small number of inevaluable patients, the accrual ceiling will be set at 100 patients in order to permit 95 registrations and 70-75 randomized patients.

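### The primary overall survival test is stated without the stratification used at randomization, and the strata are defined in two conflicting ways

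*Protocol article*

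**What the plan says.** **Randomization.** The section Stratification and Randomization uses two factors, giving four strata.

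- Risk group: the higher level is completely resected peritoneal carcinomatosis (PC) and/or ovarian metastases, with recurrent PC above 60%. The lower level is tumor perforation, then "T4 lesions that required adjacent organ resection, and/or emergency presentation with bleeding or obstructing lesions (incidence of recurrent PC < 40" percent).
- Chemotherapy: "Receiving adjuvant chemotherapy for less than 6 months vs. > 6 months".

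**Analysis.** The Statistics section restates the factors: "Patients will be stratified for synchronous peritoneal carcinomatosis and ovarian metastasis vs. perforated primary and emergency with bleeding or obstruction, and prior chemotherapy" of at most 6 months against more than 6 months. The next sentence names the primary analysis: "Kaplan-Meier curves and a two-tailed log-rank test will be the primary analysis methods". Neither stratification nor adjustment is mentioned. Cox modeling appears only later, as a secondary evaluation of prognostic factors.

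**Sizing.** The design is to "detect a difference with a 0.10 one-tailed log-rank test", with 35 patients per arm and "observation of 38 total deaths in order to have 80% power to compare the curves". Control patients are "expected to have an estimated 25% 5-year survival from the date of randomization", against a target of 50%, and "the resulting hazard ratio for the comparison of the two overall survival curves would be 1.991".

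**The concern.** Stratified randomization balances the arms on the stratification factors. If a factor predicts death, an analysis that ignores it leaves that variation in the variance estimate. The test then rejects less often than its nominal level under the null, and it loses power when treatment works. With about 38 deaths there is little power to spare.

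The stratum definition matters separately. The registration office must assign every patient to a stratum before allocation, and a stratified analysis needs those same strata. If two sections give different rules, some eligible patients have no defined level, and misassignment cannot be undone after randomization.

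**Working it through.** **1. The plan's own figure.** For 1:1 allocation, Schoenfeld's formula is d = 4(z₀.₉₀ + z₀.₈₀)² / (ln HR)², with z₀.₉₀ = 1.2816 and z₀.₈₀ = 0.8416.

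- HR 2.0 (exact from 25% and 50% at 5 years): 4 × 2.1232² / 0.6931² = 18.03 / 0.4805 = 37.5, so 38 deaths.
- HR 1.991 (rounded hazards 0.0231 / 0.0116): 18.03 / 0.4742 = 38.02, so 39 if rounded up.
- Power with 38 deaths: 80.4% at HR 2.0 and 80.0% at HR 1.991.
- Expected deaths with 60 months' uniform accrual and 24 months' further follow-up: 35 × (0.689 + 0.453) = 40.0.

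The stated figures reproduce for a plain one-sided 0.10 log-rank test. No gain from stratification was counted.

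**2. The two stratum definitions side by side.**

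| Item | Stratification and Randomization | Statistics |
|---|---|---|
| T4 with adjacent-organ resection | lower-risk level | not placed |
| PC, ovarian metastases | and/or | and |
| Perforation, emergency presentation | and/or | and |
| Exactly 6 months of chemotherapy | neither level | lower level |

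T4 with en bloc resection qualifies a patient on its own (Inclusion Criteria, item 3), so a patient eligible only that way has no level under Statistics. A patient with exactly 6 months of chemotherapy has no level under Stratification and Randomization. Neither section, read literally, places everyone.

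**3. Power with and without stratification.** From the plan: 70 patients, 1:1, the accrual and follow-up above, overall control 5-year survival 25%, one-sided 0.10. Assumed: exponential survival within strata, treatment hazard ratio 0.5 within strata, half the patients in each risk group, half in each chemotherapy level, no effect of chemotherapy duration, permuted blocks of 4 within the four strata. There were 5,000 simulated trials per row (Monte Carlo standard error of a power near 80%: √(0.8 × 0.2 / 5000) = 0.6 points). Mean deaths ran from 40 to 43.

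| Stratum death HR (assumed) | Power, unstratified | Power, by risk group | Power, by four strata | Size of unstratified test (nominal 10%) |
|---|---|---|---|---|
| 1.0 | 80.9% | 80.5% | 79.5% | 9.6% |
| 1.5 | 80.3% | 80.7% | 79.6% | 9.2% |
| 2 | 79.3% | 80.7% | 79.3% | 9.0% |
| 3 | 77.8% | 82.1% | 81.0% | 7.9% |
| 4 | 73.1% | 82.9% | 81.4% | 6.9% |
| 5 | 69.4% | 82.3% | 80.9% | 5.9% |

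Stratifying by risk group gains 0.4, 1.4, 4.3 and 9.8 points at hazard ratios 1.5, 2, 3 and 4, and costs 0.4 points at 1.0. Its size stays between 9.6% and 10.7%. A separate simulation of the same comparison gave 79.8 against 80.9%, 77.8 against 82.5% and 74.9 against 83.1% at 2, 3 and 4. With 30% of patients at high risk, the results are 79.6 against 80.5% at 2 and 77.8 against 81.8% at 3. If chemotherapy duration also carries a hazard ratio of 1.5 (risk group 3), the three tests have 77.0, 81.3 and 80.9%.

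**4. Where the stratum hazard ratio might lie.** The document gives PC incidence by group (62% and 75% against 15% and 19%, Background) but no survival by group. A rough mixture takes 13% 5-year survival with PC (Background), 25% overall and 55% developing PC (Abstract). Survival without PC is then (0.25 − 0.55 × 0.13) / 0.45 = 0.40, an assumption because these figures come from different settings.

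- 62% against 19%: survival 0.233 and 0.349, so HR = ln 0.233 / ln 0.349 = 1.4.
- 75% against 15%: survival 0.198 and 0.360, so HR = ln 0.198 / ln 0.360 = 1.6.

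Assuming 60 to 80% survival without PC instead gives hazard ratios of about 1.75 to 3.4, and a loss of roughly 0 to 6 points.

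**5. If 25% against 50% holds overall.** Mixing risk groups dilutes a within-stratum hazard ratio of 0.5, so step 3 tests a somewhat weaker alternative than the plan's. Setting the overall contrast to 25% against 50% gives these powers, unstratified against risk-stratified: 82.6 and 82.2% at stratum hazard ratio 1.5, 82.6 and 83.8% at 2, 86.6 and 90.3% at 3, 88.7 and 93.6% at 4, and 90.0 and 95.9% at 5.

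**The case against.** The article never says the test is unstratified. It is a condensed account, the factors are listed in the sentence just before the test, and a fuller protocol or analysis plan could specify a stratified log-rank. That stands: this part asks for the test to be stated and is not a proven error. Still, the only test described carries no stratification, and the sizing agrees with that.

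A reader might also infer that the trial ignores a very strong predictor of survival and so forfeits power it has already paid for. The documents do not support that. The figures above 60% and below 40% are incidences of recurrent PC, whereas the endpoint is death. Only patients still free of disease 11 to 14 months after surgery are randomized. The planned 80% did not rely on stratification, and if the stated 25% against 50% holds overall, the unstratified test keeps 83 to 90% power at stratum hazard ratios of 1.5 to 5. A loss of several points requires a stratum hazard ratio of about 3 or more.

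On the strata, the defence is that Statistics merely abbreviates the operative section. That explains the missing T4 category. It does not settle the 6-month boundary, where the operative section itself has the gap.

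**Conclusion.** The point holds in two parts.

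The conflict between the stratum definitions is established from the text and needs no assumption. It affects how patients are allocated.

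The primary test as stated does not use the randomization strata. It remains valid: the error is on the conservative side, with true size about 9% at a stratum hazard ratio of 2 and 8% at 3, against a nominal 10%. The loss of power is about 0 to 1 point at 1.5 to 2, about 4 at 3 and about 10 at 4, given a treatment hazard ratio of 0.5 within strata. The document's own figures, roughly combined, point to 1.4 to 1.6, where the loss is close to nil, but they cannot exclude larger values. Stratifying by risk group is therefore inexpensive protection and not a repair of a demonstrated shortfall.

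The mismatch between a two-tailed test and one-tailed sizing in the same section is a separate matter.

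**What to change.** - **Primary test.** State a log-rank test stratified by the risk group used at randomization. Report the hazard ratio from a Cox model stratified the same way, and keep the unstratified test as a sensitivity analysis.
- **Number of strata.** Do not require all four. With chemotherapy duration not prognostic, four strata gain nothing over the unstratified test at hazard ratios up to 2, and they stay 1 to 1.5 points below stratification by risk group alone.
- **Stratum definition.** Use one definition in both sections that places every eligible patient. For example: T4 with adjacent-organ resection in the lower-risk level, as Stratification and Randomization has it; *and/or* throughout; and at most 6 against more than 6 months, as Statistics has it. It should also say which level takes a patient with features from both lists.

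The cost is wording only, ideally settled before the first randomization. The statistical downside is about 0.4 points of power if risk group turns out not to predict survival.

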#### Post-randomization surveillance for both arms

Follow-up will commence from randomization and will occur every 3 months for two years. After two years, follow-up will be extended to every six months, and after an additional three years, follow-up will be yearly. At any stage between these follow-ups additional evaluations will be conducted as clinically indicated. At each evaluation patients will undergo: Physical examination; laboratory tests; tumor markers; CT scan of the chest, abdomen and pelvis; PET as medically indicated. Patients on both arms who develop intra/extra-abdominal metastases will be offered standard of care surgery when indicated and/or referred to their treating physician or Medical Oncology Branch, NCI, for systemic therapy.

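### Randomized patients judged grossly inevaluable are dropped from the final survival analysis; the exclusion is unnecessary and leaves the primary comparison open to bias of unknown size and direction

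*Protocol article*

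**What the plan says.** The Statistics section of the protocol article opens the sentence with the right principle, "Patients will be analyzed as randomized", and then qualifies it: "only patients found to be grossly inevaluable for any reason will not be included in the final analysis once randomized".

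Two other statements in that section use the same notion. The sizing sentence says that "a total of 35 evaluable subjects per arm (70 total) will need to be randomized". The accrual paragraph says: "Allowing for a very small number of inevaluable patients, the accrual ceiling will be set at 100 patients", and that ceiling is meant to yield 95 registrations and 70 to 75 randomized patients. Neither statement excludes anyone by itself.

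The primary objective is overall survival by randomized arm. Statistics expresses the assumed survival from the date of randomization. The section on post-randomization surveillance says for both arms: "Follow-up will commence from randomization".

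**The concern.** The second half of the sentence takes back part of the first. It acts after randomization, on the final analysis, and sets no limit on the reason.

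For death from any cause, inevaluable has no natural meaning. A patient who declines surgery, is operated on late or is lost to follow-up still has a survival time, observed or censored.

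The arms are laparotomy and surveillance without surgery. The article does not use the term open-label, but masking is not possible with these arms. Some events exist in one arm only: Stratification and Randomization sets a two-week limit for treatment after randomization in the second-look (MSLS) arm alone. The article does not call such events inevaluability, but the clause would allow it.

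If exclusions depend on both arm and prognosis, the groups compared are no longer those that randomization formed. The planned analysis rests on 38 deaths, so a few removals can matter.

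**Working it through.** **Inputs from Statistics.** 35 per arm; 5-year survival 25% (control) and 50% (MSLS), with exponential hazards 0.0231 and 0.0116 per month; hazard ratio 1.991; accrual 60 months plus 24 months of follow-up; one-sided level 0.10; power 80%; 38 deaths.

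**Reproducing the plan's figure.** Schoenfeld's formula is d = 4(z₀.₉₀ + z₀.₈₀)² / (ln HR)².
- HR 1.991: 4 × (1.2816 + 0.8416)² / 0.6886² = 18.03 / 0.4742 = 38.0. Power with 38 deaths is 0.7998.
- HR 2.00 (unrounded hazards): 18.03 / 0.4805 = 37.5.

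The chance of death by the cut-off is 1 − (e^(−24λ) − e^(−84λ)) / (60λ). It is 0.689 for control and 0.453 for MSLS, so 35 × (0.689 + 0.453) = 40.0 deaths are expected. The stated 38 deaths and 80% power are sound.

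**How many exclusions the plan expects.** 100 − 95 = 5, counted over all enrolled patients including the lead-in. Pro rata this is 5 × 35/100 = 1.75 per arm. No figure is given for randomized patients by arm.

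**Effect on the false-positive rate.** Trials were simulated with no true effect: hazard 0.0231 in both arms, uniform entry over 60 months, cut-off at 84 months, unstratified log-rank test, and 5,000 or more trials per scenario. The numbers and kinds of exclusion are assumptions. The last two columns refer to a two-sided 0.10 test.

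| Patients removed | One-sided 0.10 error | MSLS-favouring tail (nominal 0.05) | Two-sided total (nominal 0.10) |
|---|---|---|---|
| None | 0.10 | 0.05 | 0.10 |
| 1 to 5 MSLS patients, unrelated to outcome | about 0.10 | about 0.05 | about 0.10 |
| 2 earliest deaths from each arm | 0.11 | 0.06 | 0.11 |
| Earliest MSLS death | 0.13 | 0.07 | 0.11 |
| 2 earliest MSLS deaths | 0.16–0.17 | 0.09 | 0.12 |
| 3 MSLS deaths at random | 0.14–0.15 | 0.07–0.08 | 0.11–0.12 |
| 3 MSLS patients with 3 times the hazard (equally many such patients kept in control) | 0.16 | 0.08 | 0.11 |
| 3 earliest MSLS deaths | 0.21 | 0.12 | 0.14–0.15 |
| 5 earliest MSLS deaths | 0.30 | 0.19 | 0.20 |

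Three of 35 is 8.6% of an arm. By symmetry, the same removals from the surveillance arm would bias the result against MSLS.

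Both tests are shown because the sizing is to "detect a difference with a 0.10 one-tailed log-rank test", while the same section says that "Kaplan-Meier curves and a two-tailed log-rank test will be the primary analysis methods". That mismatch is a separate matter.

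**The case against.** **The clause is narrow.** Non-compliance is covered by the as-randomized principle, the exception is confined to gross cases, and very few are expected. Nothing says that an untreated patient is inevaluable, and a patient with a recorded death is the clearest case of an evaluable one. This stands as an argument about likely size. It does not defend the clause: the small number is an expectation used to set the accrual ceiling, not a cap, and the reason is left open.

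**The article is condensed.** Who decides, when and by what criteria may be in the full protocol. That is accepted, and the lack of a definition is not the point. The point is the rule that the article does state.

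**Two stronger readings are not supported.**
- A reader might infer that the clause doubles the false-positive rate in favour of MSLS. Among the scenarios with up to three exclusions, only removal of the three earliest deaths from MSLS alone does so, and then only for the one-sided error or the MSLS-favouring tail. The two-sided total doubles only with five. The article offers no basis for that number or that direction.
- A reader might infer that operative deaths escape the analysis, because Stratification and Randomization says that "patients who are randomized to the MSLS arm will be entered on stage 2 upon recovery from the operative procedure". Stage 2 is a label for where a patient is in the trial, and nothing ties the survival analysis to entering it. Survival and follow-up are both counted from randomization elsewhere in the article.

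**Conclusion.** The concern holds in a limited form. The article fixes an exclusion after randomization that overall survival does not need and that qualifies its own as-randomized principle. In a trial that cannot be masked, the judgement could depend on arm and prognosis and bias the comparison either way.

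The size is conditional. Exclusions unrelated to outcome do no harm to the error rate, and similar removals in both arms do little. One or two exclusions per arm, about what the plan's own allowance implies, would raise the one-sided 0.10 error to about 0.13 to 0.17 if they were the earliest deaths and all in MSLS. Doubling requires a more extreme pattern. These figures rest on exponential survival, the control hazard in both arms and assumed exclusions.

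This should be fixed. It does not show that the trial's result would be wrong.

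**What to change.** Replace the exclusion clause in Statistics with:

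*All randomized patients are included in the primary overall survival analysis in the arm assigned, with time counted from randomization and censoring at last contact, whatever treatment was received; any evaluable-patient analysis is a sensitivity analysis only.*

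This restores the nominal error rate in the simulation (about 0.10 one-sided). The calculation of 38 deaths and 80% power is unchanged, and no patients are added. The cost is one sentence of wording and slight dilution of the effect by patients who do not receive the assigned treatment. The stage description in Stratification and Randomization needs no change.
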